### Sample size

The sample size was estimated using G*power of 3.1.9.6 (www.gpower.hhu.de) [43–44], with the following parameters: effect size (*d*) = 0.86, α = 0.05 (two tails), power (1–β) = 90%, and allocation ratio n2/n1 = 1. The effect size was determined based on the result of our pilot study. The sample size in the current study should be 60 (30 in each group) after calculation. Considering a 10% dropout rate, a total of 66 patients are aimed to be recruited finally.

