#### Imaging data analysis.

MRI preprocessing and statistical analyses of all images will be implemented on MATLAB2021b (https://ww2.mathworks.cn) using statistical parametric mapping software (SPM12, https://www.fil.ion.ucl.ac.uk/spm/software/spm12/).

The processed data from DTI, rs-fMRI, and ASL will be employed to evaluate cerebellar stimulation’s effect on aphasia recovery in terms of structure, function, and perfusion. For the DTI data, variations in the cerebral-cerebellar loop’s structure will be identified between different groups and pre-/post treatment using Tract-Based Spatial Statistics (TBSS) analysis. With rs-fMRI, the analysis of amplitude of low-frequency fluctuations (ALFF), regional homogeneity (ReHo), and functional connectivity density (FCD) will be completed to assess the local and global functional connectivity inside the language networks. Using ASL sequences, the cerebral perfusion for every participant will be calculated, targeting the perfusion alteration, particularly the lesion area. One-way ANOVA will be performed to compare the imaging parameters among the groups (pre-vs. post-treatment, real vs. sham treatment). A linear regression analysis will be applied to establish the relationship between behavioral performance and the parameters. Any differences among these conditions are regarded as significant when the P-value is < 0.05 at the voxel level, with an FDR cluster-corrected P-value < 0.05 (two-tailed).

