### Expected conclusions

(1) Following treatment, language and non-verbal cognitive functions in the rTMS group are expected to exhibit better performance compared to those in the sham group.(2) Changes in spontaneous neural activity within the fronto-thalamic-cerebellar circuit and enhancement in perfusion within the lesion site are anticipated following the stimulation therapy.

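### Forming clusters at voxel P < 0.05 means the stated 5% cluster FDR is not reliably held if SPM12's random-field P-values are used, and it weakens regional claims

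*Protocol article*

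**What the plan says.** Protocol article, Statistical analysis, Imaging data analysis: all images are processed and analysed "using statistical parametric mapping software (SPM12", in MATLAB. For resting-state fMRI, "the analysis of amplitude of low-frequency fluctuations (ALFF), regional homogeneity (ReHo), and functional connectivity density (FCD) will be completed"; ASL gives perfusion, and DTI is analysed by TBSS. One decision rule covers all of these: a difference is "significant when the P-value is < 0.05 at the voxel level, with an FDR cluster-corrected P-value < 0.05". The sentence ends by calling the tests two-tailed. The voxel P-value is not described as corrected, and no permutation method is named.

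Discussion, Expected conclusions, states what the imaging should show: "Changes in spontaneous neural activity within the fronto-thalamic-cerebellar circuit and enhancement in perfusion within the lesion site are anticipated".

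**The concern.** Where a voxel threshold is paired with a cluster-level correction, the voxel threshold is normally the height at which clusters are formed. Random-field cluster-extent P-values rest on a high-threshold approximation and on a spatial correlation of Gaussian shape. A height of P < 0.05 is low, so the approximation is weak there, and modest long-range correlation in the noise produces large chance clusters.

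The imaging measures are declared secondary outcomes and carry the trial's account of mechanism. A false cluster would be read as the way rTMS works. In addition, a cluster-extent test says only that some effect lies somewhere inside the cluster. The lower the forming height, the larger a cluster must be to pass, and the less it says about a named circuit or the lesion site.

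**Working it through.** **The figure to reproduce.** The plan states a cluster FDR of 5%. If no effect exists anywhere, every detected cluster is false, so the FDR equals the chance of at least one detected cluster. That can be simulated.

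**Inputs from the document.** Voxel P < 0.05; cluster FDR 0.05; two-tailed; SPM12; 30 patients per arm (Sample size section).

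**Assumed inputs.** Search volume, voxel size, smoothness (FWHM) and shape of the spatial correlation. The article gives none of them.

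**Formulas, for voxel height u:**
- Expected cluster size: E[n] = FWHM³ × (1 − Φ(u)) / {(4 ln 2)^1.5 (2π)^−2 (u² − 1) exp(−u²/2)}
- Cluster P-value: P(n ≥ k) = exp(−β k^(2/3)), with β = (Γ(2.5)/E[n])^(2/3)
- FDR step: Benjamini-Hochberg across clusters

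**Step 1: error rate.** Chance of any false cluster, both tails tested, two-sided voxel P < 0.05 (u = 1.96):

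| Set-up | Gaussian correlation | Long-range share added | Clusters formed at 0.001 |
|---|---|---|---|
| A. Two-sample t maps, 30 vs 30, 3 mm voxels, 9 mm FWHM | 3.5% | 24% (20% share, 24 mm) | 5% Gaussian; 5% long-range |
| B. Z fields, 50×60×50 voxels, FWHM 3.5 voxels, FDR 0.025 per tail | 4.8% | 24% (10% share); 56% (20% share) | 1.7% Gaussian; 6.8% and 13.7% long-range |
| C. 3 mm voxels, 9 mm FWHM, 10–20% share | 8–9% | 16–23% in masks of 110–290 cm³; 29–46% in 1,944 cm³ | 3–8% |
| D. Z fields, FWHM 3 voxels, 10–20% share | 11% | 38–63% | 4% Gaussian; about 8% long-range |

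A used 400 maps per scenario and B 600 fields, so the Monte Carlo standard error near 5% is about √(0.05 × 0.95/400) = 1.1 points for A and √(0.05 × 0.95/600) = 0.9 points for B. The 0.001 column takes 0.001 in each tail (u = 3.09 in B). Testing one tail only, B gives 2.5%, 7.8% and 11.8% in that column.

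The plan's 5% is reproduced only in A and B with exactly Gaussian correlation and a two-sided voxel threshold. If the voxel threshold is instead 0.05 per tail (u = 1.645), the rates rise to 9% (Gaussian) and 38% (20% share) in A, and to 17%, 59% and 90% (0, 10 and 20% share) in B.

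**Step 2: smallest cluster that passes.** This uses the family-wise criterion at 5%: P(n ≥ k) = −ln(0.95)/E[m], hence k = (−ln P/β)^1.5, where E[m] is the expected number of clusters. Set-up B has 150,000 voxels and an estimated FWHM of 3.49 voxels:

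| u | E[m] | E[n] | β | P needed | k (voxels) | at 3 mm (× 0.027 cm³) |
|---|---|---|---|---|---|---|
| 1.645 | 224.9 | 41.3 | 0.101 | 0.000228 | 754 | 20.4 cm³ |
| 1.96 | 197.7 | 21.9 | 0.155 | 0.000259 | 390 | 10.5 cm³ |
| 3.09 | 31.3 | 5.05 | 0.411 | 0.00164 | 62 | 1.7 cm³ |

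Ratios to the 0.001 threshold: 390/62 = 6.3 for the two-sided threshold and 754/62 = 12.2 for 0.05 per tail.

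**The case against.** - **The inference engine is inferred.** The article names SPM12 but does not say how cluster P-values are obtained. If they come from permutation, the error-rate part falls. The point is therefore conditional. Random-field P-values remain the natural reading, and permutation would not make the clusters smaller.
- **The size of the excess rests on assumed inputs.** For the same 20% share, A gives 24% and B 56%. A reader might infer that half or more of null analyses would yield a false cluster. The document does not support that or any other single figure.
- **The larger figures use 0.05 per tail.** The rule is marked two-tailed, so the two-sided voxel threshold is the fairer reading and leads here.
- **The search volume may be smaller.** The section speaks of language networks, the cerebral-cerebellar loop and the lesion area, while B's box (150,000 × 0.027 = 4,050 cm³) is larger than a brain. In restricted masks the long-range rate is still 16–23%. Absolute extents do fall: cutting E[m] tenfold gives (5.954/0.1546)^1.5 = 239 voxels at u = 1.96 and (4.111/0.4109)^1.5 = 32 at u = 3.09. The ratio, about 7.5, does not.
- **DTI.** A reader might extend the error rates to every modality. TBSS tests a thin white-matter skeleton, and smooth three-dimensional fields say nothing about it. The significance sentence covers DTI; these numbers do not.
- **Localisation is a matter of degree.** A reader might infer that clusters formed at P < 0.05 cannot localise and those formed at 0.001 can. No cluster-extent test localises within its cluster. Expected conclusions also states expectations, not a decision rule.
- **P < 0.001 is not perfect.** It reached 13.7% under the heaviest tail in B, though it was well below the P < 0.05 result in every long-range scenario.

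**Conclusion.** The concern holds in a conditional form. If cluster P-values come from SPM12's random-field method, the stated 5% cluster FDR is not reliably held at a forming threshold of P < 0.05. With a two-sided threshold and both tails tested, the simulated rate is roughly 3.5–11% under Gaussian correlation and 16–63% with a 10–20% long-range share, against roughly 2–14% at P < 0.001. Volume, smoothness and tail weight are assumed, so the direction is firm and the size is not. The figures concern ALFF, ReHo, FCD and ASL only.

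The second part does not depend on the error rate: in the modelled volume, passing clusters must be about 6 to 12 times larger than at P < 0.001, which weakens regional conclusions without ruling them out.

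This is a threshold that the article fixes, not a detail left to an unseen plan. It affects secondary imaging outcomes in a trial that describes itself as preliminary. Nothing here touches the WAB outcome, the sample size or safety.

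**What to change.** Replace the significance sentence with one of this kind: clusters are formed at an uncorrected voxel-level threshold of P < 0.001 and are significant at cluster-level FDR-corrected P < 0.05 (two-tailed). State how the two tails are handled and how cluster P-values are obtained, separately for the TBSS skeleton.

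If P < 0.05 is kept as the forming threshold, obtain cluster P-values by permutation: arm labels for real versus sham, sign-flipping of within-patient differences for pre versus post. Because permutation does not cure the extent problem, also limit regional claims. Maps at P < 0.05 may be shown as descriptive figures.

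The cost is one sentence and one software setting, or some computing time for permutation. The real price of P < 0.001 is less sensitivity to weak, diffuse effects. By the Trial status section, data collection is expected to run to June 2029, so the change can be made before the final analysis.

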### Data collection and management

#### Data collection.

Data collection will be directly performed using either paper forms or specific evaluation tools. The content of each case report form (CRF) will align with and originate from the original files. The investigator bears the responsibility of ensuring the authenticity, thoroughness, and accuracy of all data. All items in the CRF must be completed, with no blanks or omissions; a slash will signify items with no records. Any corrections will be underscored, with the updated data annotated alongside the reason for the change then signed and dated by the employee making the correction. Erasing or overwriting the original record is strictly prohibited.

#### Data management.

Data originality, including documents, test reports, study summaries, and clinical trial outcomes will be archived in an electronic capture system. The archive room will ensure an organized storage and quick retrieval of all original data, test reports, protocols, and summaries. Participant privacy will be shielded by excluding their names from the CRF. Identification codes will be used by investigators to acknowledge participant identifiers and duly record them.

#### Data monitoring.

Upon review, the inspectors will assess adherence to all applicable rules, good clinical Practice, and the study protocol. They will verify the accuracy, completeness, and consistency of source documents of all CRFs while ensuring the absence of both data omissions and errors. This process involves cross-referential checks between the contents of the CRFs and the original files, effectively ensuring data uniformity. This process is known as source data verification.

#### Protocol violation.

The study protocol’s specified requisites must be meticulously followed. Whether intentional or accidental, any departure from the study protocol or good clinical practice will be classified as a protocol violation. If the deviations occur, the investigator or supervisor will complete a protocol violation record. Information regarding the discovery, process, reasons and corresponding resolution of the event will be documented, signed by the investigator, and submitted to the ethics committee.

#### Data release.

Approval from the principal investigator must be attained before any study-related articles or reports are published.

### Trial status

Participant recruitment commenced on June 1, 2026, and is expected to be completed by December 31, 2028. Data collection is expected to be completed by June 1, 2029. The research results are expected to be released by December 31, 2029.

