**Methods:**

Our study will recruit sixty-six PSA patients, who will be randomly divided into either a real or a sham rTMS group with equal distribution. The real rTMS group (n  =  33) will receive rTMS treatment over the right cerebellar hemisphere along with speech-language therapy (SLT), while the sham group (n  =  33) will receive sham stimulation and SLT. We will assess the outcomes at five intervals: before rTMS treatment, 2, 12, and 24 weeks, and 1-year post-treatment. The primary outcome in this research is the change in performance of the West Aphasia Battery from baseline to the final follow-up. Secondary outcomes include alterations in the structure, function, and perfusion neuroimaging data, as well as changes in non-verbal cognitive functions, measured using the Loewenstein Occupational Therapy Cognitive Assessment over time and between the groups. Any adverse event related to rTMS therapy will also be recorded. The results of this trial will provide insights into whether cerebellar rTMS stimulation (1) improves language function recovery in subacute phase PSA patients; (2) strengthens the functional connection of the cerebro-cerebellar network, and (3) enhances aphasia treatment outcomes by improving non-linguistic cognitive functions. We commenced patient recruitment for this trial in June 2026, and it is currently in progress.

**Registration** This project was prospectively registered at the Chinese Clinical Trial Registry (ChiCTR2600125453).

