### Interventions

Participants will receive rTMS treatment by a same magnetic stimulator (model: YRD CCY-I, Wuhan Yiruide medical equipment New Technology Co., Ltd.). The targeted location is the right cerebellum, specifically 1 cm below the occipital tuberosity and 3 cm above the right paraspinal opening. rTMS treatment takes place at this spot utilizing an 8-shaped coil (9.2 cm in outer diameter), positioned fixedly and tangent to the scalp. The stimulation parameters include a frequency of 5 Hz, intensity set at 110% of the resting motor threshold (RMT) of the contralateral cerebral hemisphere, a duration of 5s, 25 pulses, a string interval of 20s, a session time of 20 min, 48 repetitions, totaling 1200 pulses [45–46]. In the sham stimulation group, the body surface positioning points and stimulation parameters are identical to those in the real rTMS group. However, the coil is positioned perpendicular to the scalp. Participants will receive treatments once a day for 20 minutes, five days a week, over a two-week period. Additionally, both groups will undergo conventional language rehabilitation training, with each session lasting 30 minutes and conducted twice a day.

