### Outcome measurement

Outcome measures will be assessed across five time points: prior to rTMS treatment (T0), and at 2 weeks (T1), 3 months (T2), 6 months (T3), and 1 year (T4) post-treatment. The primary outcome is the evaluation of language function. Neuroimaging data, along with evaluations of non-linguistic cognitive functions, will serve as secondary outcome measures (Table 1).

**Table 1 pone.0354837.t001:** Outcome measures.

Outcome measures
**Primary outcome measures** ● WAB for determining the presence of aphasia and assessing language dysfunction recovery and deterioration.
**Secondary outcome measures** ● Imaging data for evaluating the structural, function and perfusion alterations in brain area. ● LOTCA for assessing nonverbal cognitive function.
**Safety outcome** ● Incidence of adverse events. ● VAS for assessing headache symptoms. ● FSAS for assessing fatigue symptoms.

Abbreviation: WAB: West Aphasia Battery; LOTCA: The Loewenstein Occupational Therapy Cognitive Assessment; VAS: Visual Analog Scale; FSAS: Fatigue Self-Assessment Scale.

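### The stated end of data collection is too early for the one-year primary endpoint in patients enrolled after mid-May to 1 June 2028

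*Protocol article*

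**What the plan says.** Three statements in the protocol article's Trial status section set the calendar:

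- Recruitment: "Participant recruitment commenced on June 1, 2026, and is expected to be completed by December 31, 2028".
- End of data collection: "Data collection is expected to be completed by June 1, 2029".
- Results: "The research results are expected to be released by December 31, 2029".

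The endpoint is set elsewhere. The Methods part of the Abstract states: "The primary outcome in this research is the change in performance of the West Aphasia Battery from baseline to the final follow-up". Outcome measurement lists the later visits as "3 months (T2), 6 months (T3), and 1 year (T4) post-treatment", and Study design gives the same schedule. Under Interventions, treatment is given "five days a week, over a two-week period", so a year counted from the end of treatment starts about two weeks after enrolment.

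No section shortens follow-up for late enrollees or sets a common closing date with variable follow-up.

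**The concern.** With a one-year primary endpoint, data collection has to stay open for at least a year after the last patient enters. Here it stays open for five months. If recruitment used its full window and all three dates were kept, late enrollees would have no T4 value for a purely administrative reason. The 10% dropout allowance, six patients, was not sized for that. The long-term efficacy objective in the Introduction depends on the same visits.

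**Working it through.** **Inputs.** From Trial status: recruitment 1 June 2026 to 31 December 2028, data collection to 1 June 2029, results by 31 December 2029. From Outcome measurement: T4 at one year. From Interventions: two weeks of treatment. From Sample size: d = 0.86, two-sided α = 0.05, power 90%, 30 per group, 66 recruited. The accrual pattern is not given and is assumed below.

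**The plan's own sample size.** For a two-sample t-test with n per group, the noncentrality is d√(n/2), on 2n − 2 degrees of freedom. At n = 30 it is 0.86 × √15 = 3.33, and power is 0.906. At n = 29 power is 0.896. So 30 per group reproduces, and 60 × 1.10 = 66. The sample size is not in dispute.

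**Calendar.**

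- Recruitment window: 945 days, both ends counted.
- 31 December 2028 to 1 June 2029: 152 days, or 5.0 months.
- T4 for the last possible patient, year counted from enrolment: 31 December 2029. This is 213 days after data collection closes and the same day results are due.
- T4 for that patient, year counted from the end of treatment: 31 December 2028 + 14 + 365 days = 14 January 2030. This is 227 days after closure and two weeks after results are due.
- Latest enrolment that reaches T4 by 1 June 2029: 1 June 2028 on the first count, 18 May 2028 on the second.

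**Share enrolled too late for T4.** Let f be the fraction of the recruitment window after the latest workable enrolment date: 213/945 = 0.225, or 227/945 = 0.240.

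| Accrual assumption | Formula | Share without T4 |
|---|---|---|
| Full by mid-May 2028 | none late | 0% |
| Linear decline to zero | f² | 5% to 6% |
| Uniform | f | 22.5% to 24.0% |
| Linear rise from zero | 1 − (1 − f)² | 40% to 42% |

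Under uniform accrual, 66 × 0.225 = 14.9 and 66 × 0.240 = 15.9, so 15 to 16 patients.

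**Illustrative power.** This takes uniform accrual, an analysis of patients with observed T4 only, and d = 0.86 at T4.

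- No other dropout: 66 × (1 − f) = 51.1 or 50.1 patients, 25.6 or 25.1 per group. Power is 0.854 or 0.847.
- With the planned 10% dropout as well: 46.0 or 45.1 patients, 23.0 or 22.6 per group. Power is 0.814 or 0.806.

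**The case against.** The strongest reply is that these are forecasts in a status note. Each future milestone is given as expected, and the recruitment end is an outer bound. Nothing says that the database locks on 1 June 2029 or that late enrollees forgo T4. Study design and Outcome measurement schedule T4 without exception, and the Protocol violation section treats any departure from the protocol as a violation. A slip in the dates, with every patient still followed for a year, is at least as likely as truncated follow-up.

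That stands against a stronger reading. A reader might infer that the plan will discard the primary outcome for about a quarter of the cohort, and that power is therefore 81%. The documents do not support this:

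- They show dates that cannot all be met, not a decision to drop visits.
- The quarter rests on uniform accrual, which is nowhere stated.
- The 81% also needs a complete-case analysis at T4. The Behavior data analysis section states intention-to-treat, and the handling of missing T4 values may be set in an analysis plan that is not shown.
- The effect size comes from a pilot study, and Sample size does not say which visit it refers to.

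The start of the one-year clock is also open. Outcome measurement counts from treatment, while Trial innovation places the first follow-up at the end of the second week, which could mean counting from baseline. This moves the last T4 by 14 days, and on the earlier count it falls on the results date, not after it.

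None of this removes the conflict. Calling the dates expected does not make them compatible, and both clocks put the last T4 about seven months after data collection ends.

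**Conclusion.** This is an internal inconsistency, wrong as written. The date conflict rests only on calendar arithmetic and holds on either reading of the one-year clock. The number of patients exposed does not have the same standing. It ranges from none to about 42% of the cohort according to accrual, with 15 to 16 of 66 under the uniform assumption. The power figures of about 85% and 81%, against the stated 90%, illustrate what is at stake under the listed assumptions and are not a prediction.

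**What to change.** Amend Trial status so that data collection ends no earlier than the last patient's T4 visit. If recruitment may run to 31 December 2028, that means at least mid-January 2030, which covers both readings of the clock. The results date must move to after that point as well, because changing the data-collection date alone would still leave results due on or before the last possible T4. The cost is a later completion and a later results date, with no extra patients or procedures.

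Closing recruitment by 18 May 2028 would also reconcile the dates, but it is not the cheap option. It leaves 718 of the 945 days, so accrual would have to be 945/718 = 1.32 times as fast: about 2.8 patients a month (66 in 23.6 months) instead of 2.1 (66 in 31 months), at a single centre.
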